### Outcomes

#### Primary outcome

The primary outcome is the rate of normal hips, defined as an acetabular index lower than 25 degrees on an antero-posterior radiograph, at the age of 12 months.

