#### Secondary outcomes

The rate of normal hips, defined as acetabular index lower than 25 degrees on an antero-posterior radiograph, at the age of 24 months will be studied. Also, the relation between baseline patient characteristics and the rate of normal hips will be explored. Included patient characteristics are gender, birthweight, initial alpha angle, initial beta angle, laterality (right or left, unilateral or bilateral), history of DDH in relatives, breech presentation, swaddling, twin birth, parents/caregivers’ education level, ethnicity, range of abduction in flexion (degrees), and whether the child is the firstborn child of the parents/caregivers. Accordingly, the time to hip normalization is studied. Complications during the follow-up period will be examined. The compliance of wearing the abduction device in the abduction treatment group will be assessed using visual inspection of the abduction device and a parent/caregiver-question on the number of hours that the abduction device has been worn in the last 24 hours. Furthermore, resource use and costs will be assessed using standardized cost-questionnaires. The health-related quality of life (HRQoL) of the infant will be measured with the Visual Analogue Scale (EQ-VAS) of the youth version of the EQ-5D (EQ-5D-Y) and the Infant and Toddler Quality of Life Questionnaire Short Form (ITQOL-SF47), filled out by one parent/caregiver. Last, the HRQoL of one parent/caregiver will be measured with the EQ-5D-5L and parent/caregiver satisfaction with the treatment process will be assessed with the Visual Analogue Scale.

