### Statistical methods

Statistical analyses will be performed according to the intention-to-treat principle and per-protocol approach. The difference in rate of normal hips between active monitoring and abduction treatment at the age of 12 and 24 months will be analyzed with chi-square tests. The non-inferiority margin will be set to 10% and non-inferiority will be demonstrated if one side of the 95% confidence interval lies outside the non-inferiority margin.

A Kaplan Meyer analysis will be performed to study the time to hip normalization, with events defined as Graf I or acetabular index lower than 25 degrees at 12 months or acetabular index lower than 25 degrees at 24 months. Differences in survival curves will be studied and tested for statistical significance with the Log Rank test. The relation between patient characteristics and the rate of normal hips at the age of 12 and 24 months will be studied with prediction models. Using backward elimination, a multivariable cox regression model will be constructed. The Receiver Operating Characteristic (ROC) curve and Area Under the Curve (AUC) will be used as performance parameters, goodness-of-fit will be determined by inspection and publication of the calibration plot and publication of discrimination parameters, and internal validation of the model will be performed with bootstrapping. Compliance will be presented using descriptive analysis. The difference in the number of complications will be studied with a t-test (total number of complications) and chi-square test (number of infants with a complication). Differences in quality of life and parent/caregiver satisfaction will be determined with generalized estimated equations (GEE). The statistical analyses will be performed with SPSS version 25 (IBM SPSS Statistics for Windows; Armonk, New York: IBM Corp.).

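### The prediction models target a yes/no hip status at 12 and 24 months, but the only model named is a Cox regression with no event, censoring rule or horizon

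*Protocol article*

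**What the plan says.** The protocol article defines the outcome as a status at a fixed age. The primary outcome is the proportion of normal hips, "defined as an acetabular index lower than 25 degrees on an antero-posterior radiograph, at the age of 12 months". The 24-month outcome uses the same cut-off: "The rate of normal hips, defined as acetabular index lower than 25 degrees on an antero-posterior radiograph, at the age of 24 months".

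Under Secondary outcomes, the objective for the baseline characteristics is tied to that status: "the relation between baseline patient characteristics and the rate of normal hips will be explored". Statistical methods repeats the target: "The relation between patient characteristics and the rate of normal hips at the age of 12 and 24 months will be studied with prediction models". The next sentence names the model: "Using backward elimination, a multivariable cox regression model will be constructed". The sentence after that gives the assessment: "The Receiver Operating Characteristic (ROC) curve and Area Under the Curve (AUC) will be used as performance parameters", together with a calibration plot and bootstrap validation.

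The only definition of an event in time stands earlier in the same section, for the Kaplan-Meier analysis: "events defined as Graf I or acetabular index lower than 25 degrees at 12 months or acetabular index lower than 25 degrees at 24 months".

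**The concern.** A Cox model needs a time to an event. The stated target has none: each infant is classified once, on a radiograph taken at a scheduled visit at 12 months, and once more at 24 months. The text does not say what the Cox event is, when an infant is censored, or at which time the predicted probability is read.

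An analyst who follows the text would most naturally take the Kaplan-Meier event. The model would then describe how soon a hip first looks normal on any imaging, which is a different question from whether it is normal at 12 or 24 months. Backward elimination could keep characteristics that act on speed and drop ones that act on final status. The AUC and calibration would also have no defined outcome to be judged against. At stake is whether the published predictors answer the stated secondary objective.

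**Working it through.** The plan states no figure on this point, so there is none to reproduce. The check sets the definitions side by side, bounds the possible disagreement, and illustrates it.

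**1. Does the stated outcome have a usable event time?** The radiographs are scheduled at 12 and 24 months, each within one month (Data collection methods). Infants enter at 10 to 16 weeks of age (Eligibility criteria). If the Cox event were only the 12-month radiographic status, time from entry would run from about 52 − 16 = 36 weeks to 52 − 10 = 42 weeks, plus the visit window. That spread reflects age at entry and scheduling, not how the hip develops.

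**2. Does the Kaplan-Meier event match the stated outcome?**

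| Infant | Kaplan-Meier event | Normal at 12 months |
|---|---|---|
| Graf I early, index below 25 degrees at 12 months | yes | yes |
| Graf I early, index 25 degrees or more at 12 months | yes | **no** |
| Never Graf I, index below 25 degrees only at 24 months | yes (at 24 months) | **no** |
| Never Graf I, index 25 degrees or more at both ages | no | no |

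The disagreement runs one way. Every hip normal at 12 months is an event, but some events are not normal at 12 months. The third row disagrees only if the model is read over all follow-up. Read at a 12-month horizon it would agree, but no horizon is stated.

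**3. Ceiling at 12 months.** Both disagreeing rows contain only infants abnormal at 12 months, so their total is a ceiling. Inputs from Sample size and recruitment: 800 infants, 10% loss, rates of 80%, or 80% and 70%.

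- Evaluable: 800 × 0.9 = 720, or 360 per arm.
- 80% in both arms: 720 × 0.20 = 144 abnormal.
- 80% and 70%: 360 × 0.20 + 360 × 0.30 = 72 + 108 = 180 abnormal.

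How many of these had an earlier Graf I, or became normal by 24 months, is not in the document. No 24-month rate is given, so there is no corresponding ceiling for that age.

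**4. Illustration on assumed inputs.** The simulation used 200 runs of 740 infants, six-weekly visits and one binary characteristic. The characteristic doubles the speed of normalization but leaves the 12-month probability at 80% in both of its groups. No infant abnormal at 12 months was given an earlier event, so the misclassification of step 2 is switched off and only timing differs.

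| Model | Mean estimate | Runs with p < 0.05 |
|---|---|---|
| Cox, time to normalization | hazard ratio about 1.29 | 87.5% |
| Logistic, status at 12 months | odds ratio about 1.00 | 4% |

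In this setting, selection in a Cox model would usually keep a characteristic with no relation to normal hips at 12 months. It shows that the two models can disagree, not by how much they would here.

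**The case against.** The best defence is that the Cox sentence belongs to time to normalization. The list of characteristics under Secondary outcomes is followed directly by that endpoint, and the text speaks of prediction models in the plural but of one Cox model. The fixed-age model may have been lost when the article was condensed. This is possible, but it does not rescue the text. The Cox sentence directly follows the 12- and 24-month target and is directly followed by the ROC and calibration measures. On this reading the announced models have no method at all.

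Four stronger readings are tempting, and the document does not support them.

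- *ROC, AUC and calibration show that a binary model was meant.* They also exist for Cox models at a stated horizon. What can be said is that none is stated.
- *The Cox model counts Graf I as its event.* This is an inference. The definition is given for the Kaplan-Meier analysis only.
- *The model is meant to pick infants suited to monitoring.* No such use is stated; the relation is to be explored.
- *Leaving randomised arm and age at inclusion off the list is an error.* The list is one of patient characteristics, which arm is not, and it does not rule out adjustment. Age at entry is already confined to six weeks.

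**Conclusion.** The concern holds as a mismatch between the stated outcome and the model named. The article does not leave the model open for an analysis plan to fill in. It names one that does not fit the fixed-age status it is said to predict, and it defines neither event, censoring nor horizon.

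The consequence in step 2 of the check depends on the assumption that the Kaplan-Meier event is used. Under that assumption, the number of infants classed differently at 12 months is unknown, with a ceiling of about 144 of 720 (80% normal in both arms) or about 180 (80% and 70%). These are counts of all abnormal hips, and a reader should not take them as estimates of misclassification.

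The point is confined to a secondary, exploratory objective. The primary non-inferiority comparison does not use this model.

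**What to change.** Replace the Cox sentence with two multivariable logistic regressions, one for 12 months and one for 24 months. The outcome in each is an acetabular index below 25 degrees on the radiograph at that age. Include randomised arm as a covariate, since the infants come from two management strategies. Assess each model with the AUC, calibration plot and bootstrap validation already planned.

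The article lists 13 characteristics, or about 13 to 16 terms depending on coding; arm makes 14 to 17. With 144 abnormal hips at 12 months this is 144 / 17 = 8.5 to 144 / 14 = 10.3 per term, so the bootstrap correction matters. The same ratio cannot be worked out for 24 months.

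If predictors of speed are also wanted, keep a Cox model as a separate analysis of time to normalization, and state its event and censoring rule.

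The cost is a wording change. The data and the number of infants stay the same.

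### The secondary prediction model uses backward elimination with no stated shrinkage, so its predictions will tend to be too extreme; whether the bootstrap corrects the AUC depends on an unstated detail

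*Protocol article*

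**What the plan says.** The purpose of the models is given in the Statistical methods section of the protocol article: "The relation between patient characteristics and the rate of normal hips at the age of 12 and 24 months will be studied with prediction models". The method follows directly: "Using backward elimination, a multivariable cox regression model will be constructed". Performance is then addressed: "The Receiver Operating Characteristic (ROC) curve and Area Under the Curve (AUC) will be used as performance parameters". A calibration plot is to be inspected and published, and "internal validation of the model will be performed with bootstrapping".

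The candidate predictors are listed under Secondary outcomes: "Included patient characteristics are gender, birthweight, initial alpha angle, initial beta angle, laterality (right or left, unilateral or bilateral), history of DDH in relatives", then "breech presentation, swaddling, twin birth", then parental "education level, ethnicity, range of abduction in flexion (degrees), and whether the child is the firstborn child" of the parents or caregivers.

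The article gives no elimination threshold and mentions neither shrinkage nor penalisation. It does not say whether the elimination is rerun within each bootstrap sample, and it does not say that the selected set is held fixed.

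**The concern.** Backward elimination keeps the predictors whose estimated effects happen to be large in this sample. Estimating their coefficients on the same infants carries that luck into the model. Predicted probabilities are then spread too widely: high ones too high, low ones too low.

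A bootstrap can measure this optimism, but it leaves the coefficients unchanged unless a shrinkage step is added. A calibration plot drawn in the development data will not show the problem either, because a model fitted by maximum likelihood has a calibration slope of 1 in its own data.

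A second matter depends on how the bootstrap is run. If only the already selected model is refitted in each sample, the optimism due to selection is missed and the reported AUC is corrected too little. What is at stake is the credibility of a published model of which infants reach a normal hip.

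**Working it through.** The plan states no figure for the prediction model, so there is none to reproduce. The check uses the plan's design figures and a simulation.

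**Candidate parameters.** The list has 6 + 3 + 4 = 13 characteristics. Laterality enters twice (side; one or both hips), which gives at least 14 parameters. If education and ethnicity have three levels each (an assumption), the total is 12 + 2 + 2 = 16.

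**Infants and events.** The Sample size section gives 800 infants with 10% loss: 800 × 0.90 = 720 evaluable. It uses rates of normal hips of 80% and 70%.
- Binary outcome: the smaller class is 0.20 × 720 = 144 to 0.30 × 720 = 216. With 16 parameters that is 9.0 to 13.5 per parameter; with 14 it is 10.3 to 15.4.
- Cox model with normalisation as the event: 0.70 × 720 = 504 to 0.80 × 720 = 576 events, or 31.5 to 36 per parameter with 16 parameters.

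**Simulation.** There were 16 candidates, 6 with a true effect. Binary model: 160 replicates with 40 bootstrap samples each. Cox model: 40 replicates with 6 bootstrap samples each, so its figures are rougher. Truth was measured in independent data. The bootstrap correction is

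corrected value = apparent value − mean of (performance in the bootstrap sample − performance of that bootstrap model in the original data).

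It was run with the selected set held fixed and with the elimination repeated.

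| Scenario | Apparent | True | Fixed set | Repeated | True slope |
|---|---|---|---|---|---|
| Binary, n=720, 20% non-normal, p<0.05 | 0.695 | 0.667 | 0.684 | 0.662 | 0.84 |
| Binary, n=720, 25%, p<0.05 | 0.690 | 0.668 | 0.680 | 0.660 | 0.87 |
| Binary, n=720, 20%, p<0.10 | 0.701 | 0.669 | 0.687 | 0.665 | 0.82 |
| Binary, n=720, 20%, weaker effects, p<0.05 | 0.623 | 0.586 | 0.614 | 0.577 | 0.71 |
| Binary, n=720, 25%, weaker effects, p<0.10 | 0.633 | 0.593 | 0.619 | 0.589 | 0.70 |
| Binary, one arm, n=360, 20%, p<0.05 | 0.699 | 0.644 | 0.684 | 0.639 | 0.71 |
| Cox, n=720, 81% events, p<0.05 | 0.601 | 0.591 | 0.596 | 0.587 | 0.88 |
| Cox, n=720, 82% events, weaker effects, p<0.05 | 0.563 | 0.548 | 0.559 | 0.544 | 0.76 |

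Discrimination is the AUC for the binary rows and the C-index for the Cox rows.

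**Reading the table.**
- The slope is below 1 in every row: 0.70-0.87 binary, 0.76-0.88 Cox. This describes the selected model itself, so it does not depend on how the bootstrap is run.
- In the first row the real optimism is 0.695 − 0.667 = 0.028. The fixed-set bootstrap removes 0.695 − 0.684 = 0.011; the repeated one removes 0.695 − 0.662 = 0.033.
- Excess left after the fixed-set bootstrap: 0.680 − 0.668 = 0.012 up to 0.614 − 0.586 = 0.028 for the binary model at 720 infants. It is 0.684 − 0.644 = 0.040 with one arm only. For Cox it is 0.596 − 0.591 = 0.005 and 0.559 − 0.548 = 0.011.
- With elimination repeated, the corrected value is within 0.01 of the truth in every row, slightly below it.
- The repeated bootstrap also recovers the slope. In the first row it estimates 0.83 against a true 0.84, while the fixed-set bootstrap reports 0.95. Bootstrap slopes were not computed for the Cox rows.

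**The case against.** A reader might infer that the AUC will remain too high after validation. The documents do not support that. The article's sentence on validation neither fixes the selected set nor excludes rerunning the elimination, and with rerunning the bias disappears. A condensed article may leave such detail to the full protocol or analysis plan, so silence on it is not in itself a fault. This part of the point can only be conditional.

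A reader might also take about 144 non-normal hips as the limiting count and expect an AUC error near 0.03. The plan names a Cox model. The Kaplan-Meier analysis described just before it counts normalisation as the event, and on that basis there would be 504-576 events and a far smaller error. The article does not say which event the Cox model uses, so both sets of figures are shown.

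A third inference would be that backward elimination must be replaced by a penalised model. A further simulation, with 8 of 16 candidates null, gives little ground for insisting. At 20% non-normal, ridge had the same true AUC as elimination (0.636) and a slope of 0.98. At an assumed 10% it had 0.634 against 0.626, but a slope of 1.20, which errs in the other direction.

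Finally, the article says only that these relations will be explored. It does not say that the model will decide which infants are monitored.

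All four objections stand. They do not remove the main point: backward elimination is a stated choice, no shrinkage accompanies it, and the coefficients come out too extreme under either bootstrap and in the Cox model as well.

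**Conclusion.** The point holds in limited form. As described, the model will tend to give predictions that are too extreme, with a true calibration slope of roughly 0.70-0.87 if binary and 0.76-0.88 if Cox. If the elimination is not repeated within the bootstrap, discrimination is also overstated, by about 0.01-0.03 in AUC or 0.005-0.011 in the Cox C-index. If it is repeated, discrimination is reported about correctly, but the coefficients still need shrinking.

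These sizes rest on assumed effect sizes, predictor distributions, elimination thresholds and a count of 16 parameters. The direction was the same in every scenario run. The analysis is secondary and exploratory, and the primary non-inferiority comparison does not use this model.

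**What to change.** Add to the Statistical methods section, or confirm in the analysis plan if it is already there, that:
- the elimination threshold is fixed in advance and the whole elimination is repeated in every bootstrap sample;
- the optimism-corrected AUC and calibration slope are reported;
- the final coefficients are multiplied by that slope, and the baseline hazard (or the intercept of a binary model) is then re-estimated.

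A single penalised model containing all listed characteristics is an acceptable alternative, at the price of a longer model.

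The cost is a few lines of text and no new data. The reported AUC may be slightly lower, and software besides SPSS may be needed.

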**Fig. 1 Fig1:**
[figure not shown]
TRAM-Trial flowchart

During baseline and follow-up evaluations, physical examination consists of weight measurements, asymmetric skin fold evaluation, knee height (Galeazzi test), degrees of hip abduction in flexion, and Barlow and Ortolani tests. At the age of 12 and 24 months, physical examination consists of degrees of hip abduction and leg length evaluation. Ultrasounds will be performed every 6 weeks according to the Graf method until hip normalization or technically restricted due to the appearance of the ossific nucleus of the femoral head. For the latter case, radiographs will be obtained in further follow-up. At the age of 12 and 24 months, pelvic radiographs will be performed according to a standardized protocol. Ultrasounds and radiographs will be assessed by local pediatric radiologists at the participating centers.

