### Data collection methods

Data collection is embedded in standard-care follow-up moments according to the Dutch DDH guideline (Table 3) [17]. At the enrollment consultation, baseline patient characteristics, physical examination data, and ultrasonographic measurements will be collected by the physician or researcher. Infants and parents/caregivers will return for a consultation at the orthopedic department every six weeks (± 1 week) to collect physical examination data, ultrasonographic measurements, and data on compliance and complications, until one of the endpoints (Table 2).

Additionally, baseline cost- and HRQoL questionnaires will be sent to the parents/caregivers via email. One parent/caregiver is asked to digitally fill in the cost- and HRQoL questionnaires at baseline and after 3, 12, and 18 months. The parent/caregiver will fill in two HRQoL questionnaires, one for the infant and one for the parent/caregiver. If the parent/caregiver has not filled in the questionnaires, a digital reminder will be sent after two weeks, and the parent/caregiver will be contacted by phone after four weeks.

At the age of 12 and 24 months (± 1 month), the infants and parents/caregivers will return for a consultation at the orthopedic department to collect physical examination data, radiograph measurements, and data on complications.

All members of the TRAM-Trial team will be protocol trained for standardized evaluation of included subjects.

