## Abbreviations

TRAM: TReatment with Active Monitoring
DDH: Developmental dysplasia of the hip
HRQoL: Health-related quality of life
AVN: Avascular necrosis
EQ-VAS: EuroQol visual analogue scale
EQ-5D-Y: EuroQol five dimensions health questionnaire youth
GEE: Generalized estimated equations
ROC: Receiver operating characteristic
AUC: Area under the curve

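### The two stated complication comparisons pool events of every type and severity, so a difference in avascular necrosis could be hidden or outweighed by other events

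*Protocol article*

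**What the plan says.** The Secondary outcomes section of the protocol article gives complications one sentence: "Complications during the follow-up period will be examined". It lists no event types and no grading.

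Statistical methods then fixes the comparison: "The difference in the number of complications will be studied with a t-test (total number of complications) and chi-square test (number of infants with a", where the second test sets infants with at least one event against infants with none.

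Data collection methods gathers "data on compliance and complications, until one of the endpoints (Table 2") at the six-weekly visits. At 12 and 24 months, infants return "to collect physical examination data, radiograph measurements, and data on complications". These later visits apply to both arms.

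Interventions assigns an abduction device to every infant in one arm and none in the other, apart from infants in the monitoring arm who go on to delayed treatment.

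The Abbreviations list contains "AVN: Avascular necrosis". The term appears nowhere else in the text shown.

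Monitoring provides for recording related adverse events and reporting serious ones, but states no comparison of them by arm.

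**The concern.** A count of all complications, and a yes/no indicator for any complication, both treat one case of AVN as equal to any other event. That is a weak summary here because exposure to a device differs between the arms by design. The mix of events may therefore differ as well, and a pooled result partly reflects that mix. A serious hip complication can occur in either arm, since monitoring may be followed by delayed treatment.

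Two things can go wrong. If other events are about equally common in the two arms, they add noise and hide a real difference in AVN. If other events differ between the arms, they decide the direction of the pooled result, whatever AVN does. Either way, a reader of the trial report could not tell from these two tests whether the arms differ in the harm that matters most for the hip.

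**Working it through.** **Inputs from the article.** 400 infants per group and 10% loss to follow-up (Sample size and recruitment): 400 × 0.90 = 360 evaluable per arm. The article gives no rate for complications or AVN and so has no figure of its own to reproduce.

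**Assumed inputs.** AVN rates, and the rate b of infants with at least one other complication. Each infant's AVN status is independent of other events. In the simulation (2,000 trials per scenario), the number of other events per infant is Poisson with mean −ln(1 − b). Two-sided 5% level.

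**Case 1: other events equally common in both arms. AVN 2% abduction v 0% monitoring.**

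*AVN alone.* With 0 cases under monitoring, Fisher's test gives p = 0.062 for 5 v 0 and p = 0.031 for 6 v 0, so it needs at least 6 cases. The expected number is 360 × 0.02 = 7.2, and P(X ≥ 6) for a binomial (360, 0.02) is 0.727. The simulation gave 71-74%.

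*Any complication.* Pooled rate = 1 − (1 − b)(1 − AVN). SE = √{[p₁(1 − p₁) + p₂(1 − p₂)]/360}. Power ≈ Φ(difference/SE − 1.96).

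- b = 10%: 1 − 0.90 × 0.98 = 11.8% v 10.0%; SE = 0.0232; 0.018/0.0232 = 0.78; power ≈ Φ(−1.18) = 12%.
- b = 20%: 1 − 0.80 × 0.98 = 21.6% v 20.0%; SE = 0.0302; 0.016/0.0302 = 0.53; power ≈ Φ(−1.43) = 8%.

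| Assumed AVN, abduction v monitoring | AVN alone (Fisher) | t-test / chi-square, b = 10% | t-test / chi-square, b = 20% |
|---|---|---|---|
| 2% v 0% | about 72% | 12% / 11% | 8% / 6% |
| 5% v 1% | about 88% | 30% / 31% | 19% / 18% |
| 1% v 0% | about 16% | 6% / 6% | 5% / 5% |

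Pooled figures are simulated and count results significant in the direction of more complications under abduction. The choice of Fisher's test does not produce the loss. The uncorrected chi-square on AVN alone at 2% v 0% reached 93%, so a like-for-like comparison shows a larger fall.

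**Case 2: other events differ between the arms.**

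- AVN 2% v 0%, other events 5% abduction v 15% monitoring. Pooled: 1 − 0.95 × 0.98 = 6.9% v 15.0%. The t-test favours abduction in 95% of simulated trials, against the direction of AVN.
- AVN 2% v 0%, other events 20% v 5%. Pooled: 21.6% v 5.0%. Both tests show abduction worse in about 100% of trials, driven by the other events.
- AVN 2% abduction v 4% monitoring, other events 10% v 1%. Pooled: 1 − 0.90 × 0.98 = 11.8% v 1 − 0.99 × 0.96 = 5.0%. Both tests favour monitoring in about 92% of trials although AVN is twice as frequent there.
- The same AVN rates, other events 5% v 3%. Pooled: 1 − 0.95 × 0.98 = 6.9% v 1 − 0.97 × 0.96 = 6.9%. The AVN difference disappears.

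**What separate reporting gives.** Newcombe (score-based) 95% intervals with 360 per arm:

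- 7 v 0 cases: 7/360 = 1.9 points. The Wilson limits are 0.9% to 4.0% for 7/360 and 0 to 1.1% for 0/360, giving 0.5 to 4.0 points.
- 14 v 7 cases: 3.9% − 1.9% = 1.9 points, interval −0.6 to 4.7; Fisher p = 0.18.

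**The case against.** The strongest reply is that this is a condensed article. Lists of complications, grading and tables by type are commonly left to the full protocol or the analysis plan, and nothing in Statistical methods rules them out. That stands, and it limits the point to what the article does fix, namely two tests that ignore severity.

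A reader might infer that AVN is never analysed. The documents do not support this. AVN is the one listed abbreviation with no use in the text shown, which suggests that it sits in Table 3 or Fig. 1, neither of which is reproduced. Nor can one say that the radiographs serve only the acetabular index. Complication data are collected at the same 12- and 24-month visits, and a radiographic complication could be recorded there.

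A reader might also infer that the tests are tilted towards monitoring, in support of a claim that monitoring spares infants harm. The article makes no such claim. Its hypotheses concern non-inferiority in normal hips and cost-effectiveness. It names no device-related events, and under assumed rates the distortion can run either way.

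A third tempting reading is that the t-test is the faulty one. In the simulations the t-test and the chi-square test behave almost alike. The common problem is pooling.

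Finally, a separate AVN comparison is itself weak if AVN is rare: about 16% power at 1% v 0%. That also stands, and it is why the remedy is an estimate with an interval and not another significance test.

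**Conclusion.** The point holds in a limited form. In the text shown, the only stated between-arm comparisons of complications are two pooled tests blind to type and severity, in a design where device exposure differs by arm. Under assumed AVN rates of 2% v 0% with 360 per arm, pooling with other events at 10-20% in both arms lowers power from about 72% to about 6-12%. With unequal rates of other events, the pooled result can point away from the AVN difference. Every rate is an assumption, and the size changes with the rates chosen. The mechanism needs only that serious events are a minority of all complications. Whether AVN is handled separately elsewhere cannot be settled from the article. The primary comparison is not affected.

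**What to change.** Add to the complications text in Statistical methods:

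- AVN, assessed on the 12- and 24-month radiographs already planned, and other serious complications are reported separately by randomised arm as the number of infants affected, with a risk difference and 95% confidence interval by a score or exact method.
- The classification of complications is set before the analysts see allocation. The investigators define what counts as AVN and as serious.
- The total count and any-complication comparisons stay as supporting description and are not the sole safety comparison.

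If the full protocol or analysis plan already does this, a cross-reference is enough.

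The cost is about one paragraph and, if the case report form does not already have it, one field for AVN. No extra visits or images are needed. The drawbacks are a wide AVN interval and a complication result that may look less favourable to one arm than the pooled figure would.
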